### School and participant recruitment

A list of all Victorian schools will be stratified by LGA and a random sampling technique with replacement used to invite three primary and three secondary schools within each of the prevention and control areas (spanning 26 LGAs). For example, should all schools that have been selected at random decline to participate, then the next three schools selected at random will be invited. Written invitations will be sent to the school Principal with follow-up phone calls, emails and/or visits used to confirm participation. All students in Grade 4 and Grade 6, or Grade 8 and Grade 10, will be invited to voluntarily participate through the distribution of the plain language statement and opt-out consent form. An opt-out recruitment procedure will be used, whereby participants are only required to return a signed opt-out form if they or their parents/guardians do not want their child to participate. However, if an individual child does not wish to be measured or surveyed they do not have to participate, regardless of having a signed opt-out consent form. This study has been approved by Deakin University’s Human Research Ethics Committee (2013-095), the Victorian Department of Education and Training (2013_002013) and the Catholic Archdiocese of Melbourne, Sandhurst, Ballarat and Sale.

Environments	• Change in school policy environment • Change in school physical environment • Change in school economic environment • Change in school socio-cultural environment	Primary Schools: Be Active Eat Well Environment questionnaire Secondary schools: It’s Your Move Environment Questionnaire

### Measures

#### Primary outcome

##### Anthropometry: height weight and waist circumference

Height will be measured to the nearest 0.1 cm using a portable stadiometer (Charder HM-200P Portstad, Charder Electronic Co Ltd, Taichung City, Taiwan) and weight to the nearest 0.1 kg using an electronic weight scale (A&D Precision Scale UC-321; A7D Medical, San Jose, CA) without shoes and whilst wearing a light layer of clothing (e.g., shirt/t-shirt and shorts/long pants/skirt). Age and sex-specific body mass index (BMI) z-scores will be calculated using the World Health Organizations’ growth reference to categorize weight status [21]. Waist circumference will be taken over light clothing using the cross-over technique at the midway point between the lower costal border (10^th^ rib) and the top of the iliac crest, in the mid-axillary line, perpendicular to the long axis of the trunk [25] using a steel tape measure (Lufkin W606PM) to the nearest 0.1 cm. Waist circumference data will be used to examine abdominal obesity when mean waist circumference is greater than the 90th percentile [26] according to the International Diabetes Federation using the British age and sex-specific growth reference [27]. Two measurements will be taken for height, weight and waist and the average calculated unless a third measure be needed when a discrepancy of 0.5 cm for height and waist and 0.5 kg for weight occurs.

#### Secondary outcomes

##### Physical activity and sedentary behavior: questionnaire

After evaluating current tools to examine self-reported physical activity and sedentary behavior among youth, the School Health Action, Planning and Evaluation System (SHAPES) questionnaire was identified as an exemplar as it had previously demonstrated moderate construct validity correlations (accelerometry) for average Moderate-to-Vigorous Physical Activity (MVPA) min.d^−1^ (*r* = 0.44, *P* < 0.01) among Grade 4 to Grade 10 Canadian children [28]. This construct validity correlation is considerable given that a recent systematic review of physical activity questionnaires found median criterion validity correlations to be *r* = 0.30 to 0.39 for new questionnaires and *r* = 0.25 to 0.41 for existing questionnaires [29]. The authors of the SHAPES questionnaire were contacted and they highlighted success towards uniform/standard measurement of physical activity and sedentary behavior across Canada (in consultation with several other universities) [30]. The use of standard measures potentially enables comparisons with other studies. Therefore, three question items from the standardised Canadian Core Indicators and Measures of Youth Health – Physical Activity & Sedentary Behavior Module [30] questionnaire examining duration spent in MVPA, sedentary behavior and mode of active transport to and from school were also included alongside 15 question items from the SHAPES questionnaire examining active transport, frequency of physical education and perceived psychosocial influences on physical activity (social support and parental modelling) [28]. The SHAPES questionnaire and Core Indicators and Measures were developed in Canada and based on the Canadian physical activity [31] and sedentary behavior [32] guidelines for youth. These guidelines are identical to the Australian physical activity and sedentary behavior guidelines in recommending ≥ 60 min/day of MVPA and ≤ 2 h/day of electronic media for entertainment [33, 34]. This supports the use of these question items in the Australian context as they are likely to have similar psychometric properties among Australian youth. Through these questionnaires, duration spent in MVPA (in total) and sedentary behavior (outside of school) over the previous 7 days will be recalled by participants and adherence to Australia’s physical activity and sedentary behavior guidelines for children (5–12 years) [33] and young people (13–17 years) [34] calculated. Contextual information relating to participation (e.g., number of television units in house and active transportation) and perceived psychosocial influences on physical activity participation (e.g., social support, parental modelling) will also examined.

### Quality of life: questionnaire

Given that childhood obesity has both physical and psychological health consequences [1, 2], the assessment of health-related quality is important to capture the multidimensional state of health [39]. Although quality of life is a complex concept, a critical search of the literature supported the use of the Paediatric Quality of Life Inventory 4.0 (PedsQL)™ [40] to examine perceived health-related quality of life among participants. The PedsQL has been widely used in Australian [41–44] and international (>350 citations in Medline) studies of children and adolescents to examine health-related quality of life in a variety of settings, thus enabling accurate comparison to other studies due to the application of the same instrument. It is a quick to complete (1-page) 23-item questionnaire that examines self-rated physical health, emotional health, school functioning and social health. It has been subject to extensive psychometric testing in a variety of languages [45] with high internal consistency observed among children 8 to 11 years (α = 0.90–0.91) in the United States and validity through comparison with children with diagnosed chronic health conditions (effect size *d* = 0.63–0.72) [40]. The questionnaire includes four domains (physical health, emotional health, school functioning and social health) that will be examined individually and in combination both cross-sectionally and change over time. The scores are summed to provide an overall global health-related quality of life score as well as generating physical and psychosocial sub-scale scores.

### Depressive symptomology: questionnaire (Grade 8 and Grade 10)

Given the relationship between obesogenic risk factors (physical activity, sedentary behavior and diet) and depressive symptoms among adolescents [46], this important outcome will be examined. The Short Mood and Feelings Questionnaire (SMFQ) [47] has previously demonstrated high internal consistency among Australian children aged 10–14 years (α > 0.85) [48], with the additional benefit of having international application and validation among children and adolescents [47]. The SMFQ was selected to examine depressive symptoms as clinical diagnosis of depression through clinical psychiatric interviews is impractical for population based-studies [47]. Due to the nature of the questionnaire items, it was felt that the questionnaire be administered to secondary school students only (Grade 8 and Grade 10), despite being psychometrically tested among Australian children as young as 10 years of age [48]. The responses from the questionnaire will be collated into a SMFQ score, which will be used as a measure of depressive symptomology.

#### Demographic characteristics

Demographic characteristics of participants will be captured through the self-report questionnaire and include: date of birth, gender, residential postcode, language spoken at home, country of birth and ancestry. These characteristics will be used primarily as covariates for the primary and secondary outcome measures.

#### School environments

Within each participating school, approximately 1–3 members of staff will be invited to complete a school environment audit (Primary Schools: Be Active Eat Well Environment questionnaire Secondary schools: It’s Your Move Environment Questionnaire). This survey, examines the schools’ policies and environments in relation to physical activity and healthy eating (e.g., number and type of physical activity and healthy eating policies; types of unhealthy food available in school canteens and distance of nearest takeaway shop, frequency and duration of physical education and sport education). This survey takes approximately 15 min to complete and will be conducted during the school day (typically at recess or lunch) [49]. These questionnaires were developed for two previous community-based interventions and were examined for face validity by the study’s executive but these instruments have not been subject to formal psychometric testing due to the nature of the question items. School policy, physical, economic and socio-cultural environments will be examined for change over time and their relationship with obesity and associated risk factors.

### Data analysis

Cross-sectional (within year) and longitudinal (across region/LGA) multilevel analyses will be conducted to consider different exposure variables (condition) and the effects of clustering (within school, between LGA) and other potential confounders (age, gender, socioeconomic position). A multilevel growth model [50] will be used to examine how BMI z-score, and other dependent variables (physical activity, sedentary behavior, diet quality, wellbeing), change over the three waves of data collection. A growth model will be used because it accommodates; 1) modelling of change over time; and, 2) simultaneous modelling of change occurring within an LGA over time, and between LGAs over time.

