**Methods:**

Twenty-four geographically bounded areas were randomized to either prevention or comparison (2012). A repeat cross-sectional study utilising opt-out consent will collect objectively measured height, weight, waist and self-reported behavioral data among primary [Grade 4 (aged 9-10y) and Grade 6 (aged 11-12y)] and secondary [Grade 8 (aged 13-14y) and Grade 10 (aged 15-16y)] school students (2014 to 2018). Relationships between measured childhood obesity and system causes, as defined in the Foresight obesity systems map, will be assessed using a range of routine and customised data.

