## Methods/design

### Setting

Healthy Together Victoria, an initiative of the State Government of Victoria, was initially funded in partnership with the Commonwealth Government of Australia [17]. Victoria is a state of approximately 5.8 million people in the South-Eastern region of Australia [19]. As described above, the centrepiece of HTV is a funded workforce of approximately 170 people across the state in local government, community health and non-government organisations whom take a range of actions at the community and state level [18]. These actions are varied but can include: policy and leadership for health promotion; providing quality improvement frameworks for early childhood services, schools and workplaces; supporting policy development/implementation and targeted strategies within settings; working with food growers, producers and sellers to increase access to healthy food, especially disadvantaged populations; working with urban planning to support active transport; working with sport and recreation centres to increase healthy food access; building leadership for prevention; and social marketing of health promotion messaging www.healthytogether.vic.gov.au [18]. The cluster randomized trial, embedded within the wider HTV initiative, includes 12 prevention areas spread across 14 local government authority (LGAs) (Healthy Together Communities) and 11-matched comparison areas spread across 12 LGA’s in Victoria, Australia (with one comparison community acting as a matched comparator for two prevention areas). Matched randomisation of clusters was based on socio-demographic indices [Socioeconomic Index for Areas (SEIFA)] [20] and chronic disease risk factor prevalence (i.e., unhealthy weight)] of adults within participating LGA’s and was conducted by the Department of Health and Human Services (Victoria). The wider HTV evaluation has a multitude of components, several of which are outlined in Table 2. The methodology described here captures (1) how the core primary and secondary outcomes will be measured and (2) how these relate to community-level system change.

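### The Aim 1 models take the LGA as their top clustering level, but areas were randomised; if LGAs within an area share variance, the standard error of the condition effect is somewhat too small

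*Protocol article*

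**What the plan says.** **Unit of allocation.** The abstract states: "Twenty-four geographically bounded areas were randomized to either prevention or comparison (2012"). The Setting section says the trial "includes 12 prevention areas spread across 14 local government authority (LGAs"), against "11-matched comparison areas spread across 12 LGA’s in Victoria, Australia", "with one comparison community acting as a matched comparator for two prevention areas". The sample size section places the intervention at area level and uses 12 clusters per arm. School recruitment is also by area: "three primary and three secondary schools within each of the prevention and control areas (spanning 26 LGAs").

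**Unit of analysis.** The Data analysis section under Aim 1 names two clustering levels: "effects of clustering (within school, between LGA) and other potential confounders (age, gender, socioeconomic position"). One reason it gives for the growth model is "simultaneous modelling of change occurring within an LGA over time, and between LGAs over time". The same section once calls the longitudinal analysis *across region/LGA*, without defining region. It names no area level.

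**The concern.** In a cluster trial, the condition effect has to be judged against variation between the units that were allocated. Two LGAs in one area received the same allocation as a block. They may also share programme delivery and local trends: the Background places the funded workforce in 12 communities, not in 14 LGAs. A model whose highest random effect is the LGA treats such a pair as two independent units.

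Any variance the pair shares is then counted as if it averaged out. The standard error of the condition effect comes out too small, and the reference distribution gets more degrees of freedom than the randomisation supports. The error runs toward a false claim of benefit in the model for BMI z-score, the outcome on which the trial was sized.

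**Working it through.** **Counts**
- LGAs: 14 + 12 = 26, which agrees with the recruitment section.
- Areas by the Setting section: 12 + 11 = 23, with one comparison area serving two prevention areas.
- Areas by the abstract and the sample size: 24 (12 v 12). The plan's total reproduces with 24: 25 children × 4 year levels × 24 areas × 3 waves = 7,200. With 23 areas it would be 6,900.
- An unmatched two-sample comparison would have 14 + 12 − 2 = 24 degrees of freedom by LGA and 12 + 11 − 2 = 21 by area.

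**Inputs**
- From the sample size section: SD 0.93, intra-class correlation 0.1, and 4 × 25 = 100 children per area per wave.
- Assumed, because the article gives no map of LGAs to areas: no area holds more than two LGAs. Then two prevention areas and one comparison area hold two each.
- Assumed: a share *s* of the cluster variance is common to LGAs in the same area. The document gives no value, so *s* runs from 0 to 1.
- Proxy: a two-sample t-test on LGA means at one time point, with 100 children per LGA. This is not the planned growth model.

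**Variance terms**
- Cluster variance: 0.1 × 0.93² = 0.08649.
- Sampling variance of an LGA mean: 0.9 × 0.93² / 100 = 0.00778.

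**True variance of the difference, all variance shared (*s* = 1)**
- The shared part is weighted by the sum of squared LGA counts per area, over the squared number of LGAs.
- Prevention: (2×2² + 10×1²)/14² = 18/196 = 0.0918. Comparison: (1×2² + 10×1²)/12² = 14/144 = 0.0972.
- Variance = 0.08649 × (0.0918 + 0.0972) + 0.00778 × (1/14 + 1/12) = 0.01756, so the true SE is 0.1325.

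**Variance the LGA-level test would report, *s* = 1**
- The expected pooled variance keeps the fraction [14(1 − 0.0918) + 12(1 − 0.0972)]/24 = 0.981 of the shared part.
- Variance = (0.981 × 0.08649 + 0.00778) × (1/14 + 1/12) = 0.01434, so the reported SE is 0.1197.
- Ratio: 0.1197/0.1325 = 0.90.

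**Half shared (*s* = 0.5).** The same steps give 0.1203/0.1268 = 0.95.

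**None shared (*s* = 0).** Both are 0.1208, ratio 1.00.

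**Type I error at nominal 5%** (simulation, 200,000 null trials per row; the two rows with sharing agree with a separate run of 40,000)

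| Share of cluster variance common to the area | Reported SE / true SE | LGA as unit | Area as unit |
|---|---|---|---|
| 0 | 1.00 | 5.0% | 5.0% |
| 0.5 | 0.95 | 6.2% | 5.0% |
| 1 | 0.90–0.91 | 7.4% | about 5.0% |

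**Sensitivity to the map.** If one prevention area held three LGAs instead of two areas holding two each, the prevention weight would be (3² + 11×1²)/14² = 20/196 = 0.102. The ratio at *s* = 1 would then be 0.1194/0.1358 = 0.88. The picture does not change.

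**The case against.** **The article may use LGA loosely for the trial community.** It speaks of intervention and comparison LGAs in the Aim 1 hypotheses, equates community with LGA level under Aim 2, and writes *region/LGA* once. The authors may have meant the area. This lowers confidence that the error would reach the analysis. It does not remove the point, because both explicit statements of level in the Data analysis section say LGA, region is undefined, and the article itself counts areas and LGAs differently.

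**Nesting, random slopes and small-sample corrections belong in an analysis plan that is not shown.** That is fair for their absence, which is not the complaint. The complaint is that a level is stated and differs from the allocated unit.

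**The calculation is not the planned model.** This stands. A growth model with covariates, schools and three waves would give other figures, and none was derived for the condition-by-time term.

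Some stronger readings are tempting but not supported:
- That the standard error is certainly too small. With no shared variance there is no bias, and the document gives no figure for sharing.
- That the plan tests on 26 units or 24 degrees of freedom. It states neither. 26 appears as geography, and 24 is my subtraction.
- That 23 areas, and so 21 degrees of freedom, are settled. Two sections imply 24 areas. The 21 also ignores the matching and the shared comparator.
- That the Aim 2 condition-by-time regressions carry the same error. Aim 2 works at LGA level on purpose, and the random effects of those regressions are not given.

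**Conclusion.** The point holds as a mismatch between the stated top clustering level and the unit that was randomised and powered. Its consequence is conditional: zero if LGAs of one area share no variance, and at most about 2.4 percentage points of type I error (7.4% − 5.0%) and about 10% of the standard error if they share all of it. These figures rest on the two-LGA assumption, the plan's intra-class correlation of 0.1 and the cluster-mean proxy.

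The effect stays small because probably only three areas hold more than one LGA. A reader might call this an essential correction, since it touches the model for the main outcome. The size does not support that, and moderate severity is right. It is still worth correcting, because the remedy is almost free and restores a test based on the randomised unit.

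**What to change.** In the Aim 1 Data analysis section:
1. Name the randomised area as the highest-level random effect, with a random intercept and a random time slope, in place of LGA. Put school below it.
2. Treat LGA nested in area as optional. With 26 LGAs in 23 areas, and probably only three areas holding more than one, its variance would be weakly identified.
3. Base any small-sample degrees of freedom on the number of areas.
4. State whether 23 or 24 areas are analysed, bring the abstract, Setting and sample size sections into line, and say how the comparison area matched to two prevention areas enters the model.
5. Define *region/LGA* or drop it.

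This changes one random-effects term and needs no new data. Confidence intervals become slightly wider. It should be settled before outcome data are analysed, so that the unit is not chosen after results are seen.

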### Study design, sampling and sample size

Standard approaches for sample size calculations within cluster randomized trials were made (in GenStat V14.2) based on the comparison of Body Mass Index standardized for age and sex (BMI-z) [21] scores between intervention (12 clusters) and comparison (12 clusters) communities using power of 0.8 and 0.05 for significance test. The clustered trial involves intervention at the area level and thus an intra-class correlation of 0.1 for the BMI-z was used, based on previous school-based research [22–24]. Baseline BMI-z (0.65) and standard deviation (0.93) were taken from our previous studies of >1800 [22] school children and the expected change in BMI-z over the 4 years was set to 0.18. The justification for this estimated change over 4 years of 0.18 is based on the findings from our previous interventions within the same age groups (primary [22] and secondary students [24]) and was associated with a 3 percentage point reduction in overweight and obesity in these populations.

Using the parameters above, the sample size calculations indicated a need for ≥ 25 children in each of the 4 year levels (Grade 4, Grade 6, Grade 8 & Grade 10) to be assessed in each intervention/comparison area to determine significant differences in BMI-z score between intervention and comparison communities. A repeat cross-sectional design will assess all participating students in each grade level per intervention and comparison community and repeated samples of students on a biennial basis in 2014, 2016 and 2018 during Term 3 (Jul - Sept) of the Victorian School Term (giving a total of approximately >7,200 children assessed once).

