### Study design and sampling

In order to test the stated hypothesises, data routinely collected by the Victorian Department of Health and Human Services plus other freely available data will be used to map accepted relationships between childhood obesity and its determinants as defined by the Foresight obesity systems map at the LGA level [13]. A detailed description of the study design, sampling strategy, protocols and procedures for each of these data sources are outlined in Table 2. Table 3 provides details of the available data items that will be used in the analysis of the systems influencing obesity. The data sources contain a mixture of child and adult data. While the primary interest of this study is childhood obesity, it is obesity at an LGA level not at an individual level. Data collected only from adults such as ‘Health Literacy for Healthy Eating and Physical Activity’, 'Affective attitudes (facilitators & barriers, decisional balance) for Healthy Eating and Physical Activity’, and ‘Self-efficacy for Healthy Eating and Physical Activity’ will be used to populate parameters at the LGA level as these are seen as systems indicators. Similarly adult anthropometric data will be included in the models in order to control for the influence of adult BMI on child BMI. It would be expected that there would be a medium to strong correlation even at the LGA level between these variables. How these systems indicators plus individual level behaviors impact childhood obesity will then be tested.

**Table 2 Tab2:** Detailed description of datasets to be incorporated in Aim 2

Survey	Description (Study design, sampling and study protocol)	Participants, recruitment measures and procedures	Outcome(s) of interest	Instrument/measure

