Victorian Population Health Survey (VPHS) [58]	Established in 1998, the VPHS is a Victorian representative surveillance survey that collects detailed information on the health, lifestyle and wellbeing status of Victorian adults. Random digit dialling of registered telephone numbers was used in each study year (annually from 2001) with participants completing a computer assisted telephone interview (CATI). In 2008 and 2011/12, sampling occurred in all of the 79 LGAs within Victoria and represented baseline measures for HTV. A target sample of 426 interviews per LGA was achieved. Triennial LGA-level data collection among over 33,000 is envisaged for the duration of the HTV (2014 and 2017).	• 33,673 adults (≥18 years) in private dwellings recorded complete interviews between Sept 24 and Dec 16 2008 in HTC intervention and comparison communities • All residential households with land-line telephone connections were considered eligible for the study • Interviewers made up to six calls on different days of the week and times to establish contact with the household, which was controlled by a customised call algorithm • The average interview length was approximately 22 min. • The response rate was 64.9 %.	• Change in BMI score • Change in overweight and obesity prevalence • Change in fruit and vegetable intake • Change in the proportion meeting the Australian physical activity guidelines for adults [59]	Self-rated health status
				CATI (smoking, fruit and vegetable intake, alcohol consumption, levels of PA)
				Self-reported height and weight

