Preventive Health Survey (PHS)	The Preventive Health Survey was undertaken in 2011/12 and is again scheduled for completion in 2016/2017. The PHS furthers the information derived from the VPHS as it is able to make comparison estimates for each intervention HTV area compared to its’ matched-control area. This is in contrast to the VPHS, which can only make estimates for intervention and comparison HTV areas combined.	• ≥9,500 adults (≥18 years) and ≥ 1800 children (5–18 years) randomly sampled from HTV intervention and comparison communities	• Change in BMI • Change in overweight and obesity prevalence • Change in the proportion of participants meeting Australia’s physical activity and sedentary behavior guidelines for children (5–12 years) [33] and young people (13–18 years) [34] • Change in the proportion of participants eating the required amount of fruit and vegetables [39]	Self-rated health status CATI (PA, SB environmental amenity, perceived barriers and facilitators to healthy eating and activity)
				Self-reported height and weight
School Activity Audits	The Healthy Together Achievement Program is currently being offered to all Victorian Primary and Secondary schools. The program began in 2011, and was developed by the Department of Education and Training and Department of Health & Human Services (Victoria). The Achievement Program is designed to support schools to become health promoting schools and aide in the attainment of state-wide benchmarks for health promotion. Through participation in the Achievement program, schools provide information on the schools’ engagement in prevention efforts.	• Primary and Secondary Schools involved in the Healthy Together Achievement Program • The schools’ Achievement Program Coordinator completes the audits via the online registration system.	• Uptake and dispersion of the Achievement Program across Victoria • Change in progression through the various stages of the Achievement Program and achievement of benchmarks among HTV and comparison communities over time.	Online School Activity audit

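### The Aim 1 adjustment set omits pre-intervention area weight status, which the programme holds and expects to be prognostic, so the within-year arm comparisons are less precise than they need be

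*Protocol article*

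**What the plan says.** The Aim 1 Data analysis section plans within-year and longitudinal multilevel analyses that account for clustering and "other potential confounders (age, gender, socioeconomic position"). Demographic characteristics adds items such as home language, country of birth and ancestry as covariates. Neither section names a weight variable.

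Other parts of the article bear on this:

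- **Setting.** Areas were matched, then randomised, on SEIFA and on adult chronic disease risk factor prevalence, with unhealthy weight given as the example.
- **Table 2, Victorian Population Health Survey (VPHS).** In 2008 and 2011/12, "sampling occurred in all of the 79 LGAs within Victoria and represented baseline measures for HTV". It reports 426 adult interviews per LGA, with self-reported height and weight.
- **Table 2, Preventive Health Survey (PHS).** "The Preventive Health Survey was undertaken in 2011/12 and is again scheduled for completion in 2016/2017". It samples at least 9,500 adults and 1,800 children in trial areas and gives area-by-area estimates. The same entry says the VPHS supports estimates only for the areas combined.
- **Study design and sampling (Aim 2).** Adult anthropometry goes into the Aim 2 models as a control for child BMI: "It would be expected that there would be a medium to strong correlation even at the LGA level between these variables".
- **Background, and Study design, sampling and sample size.** The intervention began in 2012. Children are measured in 2014, 2016 and 2018.

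**The concern.** The intervention is allocated to 23 or 24 areas, so the precision of a between-arm comparison is limited mainly by variation between areas. Measuring more children barely reduces that variation; a prognostic area-level covariate can. Two of the three adjusters named in Data analysis, age and gender, are largely built into BMI-z already. Only socioeconomic position is likely to explain much of the difference between areas.

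The protocol treats area adult weight as important enough to match on and to control for in Aim 2, but leaves it out of Aim 1, which carries the randomised comparison. Because no measured wave precedes the intervention, the within-year comparisons cannot use the outcome's own baseline instead. What is at stake is wider intervals than necessary for the within-year differences in BMI-z and in overweight/obesity prevalence.

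**Working it through.** **Inputs from Study design, sampling and sample size**

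- Comparison of "scores between intervention (12 clusters) and comparison (12 clusters) communities", "using power of 0.8 and 0.05 for significance test". Sidedness is not stated; I take two-sided.
- "intra-class correlation of 0.1 for the BMI-z was used, based on previous school-based research"; SD 0.93; difference 0.18.
- At least 25 children in each of 4 grades, so m = 25 × 4 = 100 per area per wave.
- Setting gives "11-matched comparison areas spread across 12 LGA’s in Victoria, Australia", so 12 v 11 areas is also shown.

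**Assumption.** The document gives no numerical correlation. I read medium to strong as r = 0.3 to 0.7, taken as the correlation of the covariate with true area BMI-z level beyond socioeconomic position.

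**The plan's own figure.** Without clustering, n per arm = 2 × [0.93 × (1.960 + 0.842)/0.18]² ≈ 420. The design effect is 1 + 99 × 0.1 = 10.9, so 420 × 10.9 = 4,578 per arm are needed, against 12 × 100 = 1,200. The stated size is not reproduced with area as the cluster. That is a separate problem; here it only explains why the starting power is low.

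**Unadjusted level comparison**

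- Variance of an area mean = 0.93² × (0.1 + 0.9/100) = 0.8649 × 0.109 = 0.0943.
- Between-area share = 0.1/0.109 = 92%.
- SE of the arm difference = √(0.0943 × 2/12) = 0.125.
- Power (noncentral t, 22 df) = 28%.

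**Adjusted.** The between-area part is multiplied by (1 − r²), and one df is spent (21 df):

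| r | 0.1(1 − r²) + 0.009 | Variance reduction | SE | Power, 12 v 12 | Power, 12 v 11 |
|---|---|---|---|---|---|
| none | 0.109 | – | 0.125 | 28% | 27% |
| 0.3 | 0.100 | 8% | 0.120 | 30% | 29% |
| 0.5 | 0.084 | 23% | 0.110 | 35% | 33% |
| 0.7 | 0.060 | 45% | 0.093 | 46% | 44% |

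**Sensitivity 1: socioeconomic position takes part of the gain.** Suppose socioeconomic position and adult weight each correlate 0.5 with area BMI-z, and 0.6 with each other (assumed).

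- The partial correlation of adult weight is (0.5 − 0.5 × 0.6)/√[(1 − 0.25)(1 − 0.36)] = 0.2/0.693 = 0.29.
- Explained between-area variance rises from 0.25 to 0.25 + 0.75 × 0.29² ≈ 0.3125.
- The bracket falls from 0.084 to 0.07775, a further 7%. Power goes from 34.5% to 36.7%.

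**Sensitivity 2: part of the ICC lies between schools.** The ICC comes from school-based studies. Split it as 0.02 area and 0.08 school, with six schools per area (assumed split).

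- The bracket is 0.02 + 0.08/6 + 0.009 = 0.0423.
- r = 0.3 removes 0.02 × 0.09 = 0.0018, or 4%. r = 0.5 removes 0.02 × 0.25 = 0.005, or 12%.
- Power gains are about 2 and 5 points.

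**Growth model.** The condition-by-time term compares change from 2014 to 2018. An area effect that is constant over time drops out of each area's change, so a covariate that predicts only that constant part has almost nothing left to explain. It helps this term only if baseline level predicts the slope, which requires its interaction with time.

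**The case against.** The strongest objection is that the main hypothesis concerns relative change in BMI-z over the measurement period and is analysed with a growth model. The power figures above are for a level comparison at a single wave. This stands: a reader might infer that the test of the 0.18 hypothesis loses up to 18 points of power, and the document does not support that. What remains is the within-year analyses, which Data analysis also commits to.

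A reader might also infer that, without this covariate, a chance difference in prior weight between arms could pass for an effect. Matching on adult unhealthy weight limits that imbalance, so the argument is weak. Matching does not by itself return the precision to the analysis, and the Aim 1 section does not mention modelling it.

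The data source is also open to question. The VPHS, the only source called baseline, is adult and self-reported, and Table 2 disagrees with itself on whether it supports area estimates. The PHS is also self-reported, is not labelled baseline, and its 2011/12 round may overlap the 2012 start. These points affect which value to use and how strong r is likely to be; they do not remove the case for a covariate.

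The expected correlation is stated for adult and child BMI in Aim 2, not for earlier adult self-report against later measured BMI-z. That is fair, and is why r is an assumption here.

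Finally, covariate detail may sit in an unseen analysis plan, and the listed adjusters are not wrong in themselves. But the article names its adjustment variables, and the suggestion is a concrete change to that stated model.

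**Conclusion.** The point holds for the within-year Aim 1 comparisons. The named adjustment set leaves out a variable that the protocol matched on, has data for, and expects to be related to child BMI.

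If r is 0.3 to 0.7 beyond socioeconomic position and the whole ICC of 0.1 lies between areas, the variance of a within-year arm difference falls by 8% to 45%, and power rises by 2 to 18 points from 28%. At the low end the gain is minor; it becomes material from about r = 0.5. Both sensitivity checks shrink it. Within this range the adjustment does not bring power near 80%.

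For the growth model's condition-by-time term, little should be expected. The omission does not bias the randomised comparison; it costs precision.

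**What to change.** In the Aim 1 within-year multilevel models of BMI-z and overweight/obesity, add one area-level fixed covariate, named in advance: the area's pre-intervention adult overweight/obesity prevalence or mean BMI. Possible sources are the weight-risk value used for matching, VPHS 2008, or the PHS 2011/12 area estimate if it was collected before the intervention started in that area. Use no later survey round.

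Before choosing the VPHS, reconcile the two Table 2 entries: 426 interviews per LGA in one, combined estimates only in the other.

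In the growth model, enter the covariate together with its interaction with time, and state that little gain is expected unless baseline level predicts the slope.

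The cost is a sentence or two in the analysis plan, a merge of data already planned for Aim 2, and about one between-area degree of freedom in the within-year models (already charged in the figures above). With only 23 or 24 areas, keep to a single such covariate.
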